### Secondary outcome

The secondary outcomes include the following eight items (1): Treatment remission rate of ISI (40): The percentage of people with a total score of <8 points in total ISI score compared to the baseline score. It will be evaluated at weeks 4, 8 and 16. (2) SE with Sleep Diary: SE is the percentage of time spent asleep while in bed (41). It is calculated by (TST/TIB) × 100%. Sleep diary analysis will be used to determine SE subjectively which will be assessed at weeks 0, 1, 2, 3 and 4. Sleep Onset Latency (SOL), Wake After Sleep Onset (WASO), Early Morning Awakening (EMA), and Total Time in Bed (TIB) are among the sleep metrics that may be monitored using a sleep diary (41). (3) Treatment response rate of ISI at the 8th and 16th weeks of follow-up. (4) The mean changes of ISI (40) from baseline. It will be evaluated at weeks 4, 8 and 16. (5) GAD-7 (42): It is a concise anxiety self-assessment instrument consisting of 7 items to assess patients’ anxiety over the past two weeks. It will be evaluated at weeks 0 and 4. (6) PHQ-9 (43): It is a simple and validated 9-item depression self-assessment tool that assesses patients’ depression over the past two weeks. It will be evaluated at weeks 0 and 4. (7) QLQ-C30 (44): It contains 30 entries with six dimensions. It is widely used in clinical studies to assess the life quality of patients. It will be evaluated at weeks 0 and 4. (8) Sleep parameters recorded in Actigraphy (wGT3X-BT. LLC, Pensacola, USA): It provides a non-invasive monitoring method (45) that allows objective data related to sleep quality to be collected in the subject’s relatively usual and familiar natural sleep environment. It records the contents of TST, sleep awakenings (SA), WASO, average wake duration (AA) and SE, with the detection and interpretation of movements using the device’s accelerometer. We used the default settings of ActiLife for sleep situations: a sampling rate of 30 Hz in a time window of 60s (46). It will be evaluated at weeks 0, 1 and 4. (9). Weekly usage of remedial drugs: It is the percentage of participants who used emergency drugs. It will be evaluated at weeks 1, 2, 3, 4, 8 and 16.

### Blinding assessment

The independent assessor will provide participants with three choices after they have completed their last treatment: acupuncture, sham acupuncture, and uncertainty. Their choices will then be recorded. The result will be used to assess the success of the blinded implementation.

### Safety evaluation

Acupuncture’s adverse events (AEs) include the following: (1) Adverse reactions to acupuncture such as dizziness, subcutaneous hematoma, and local infection may occur. (2) Excessive acupuncture stimulation causes exacerbations. The severity of the AEs will be evaluated. Grade 1 (mild), 2 (moderate), or 3 (severe) (severe or medically significant). The investigator will assess the degrees and causes of these AEs to determine if they are connected to acupuncture or sham acupuncture. The proportion of AEs (%) during the trial is used to calculate the incidence of AEs. Any adverse event occurring during the trial should be completed on an “Adverse Event Form” and further investigated. Additionally, the process and outcome should be recorded in detail. If any serious adverse event occurs, treatment will be terminated and a final decision will be made on whether to continue the study.

### Sample size calculation

In this study, the sample size is estimated according to the treatment response rate of subjects at week 4 as the primary outcome indicator (40, 41). Based on the results of our pre-preliminary trial, the treatment response rate at week 4 was 33.3% (5/15) in the treatment group; 6.7% (1/15) in the control group; we conservatively assumed a treatment response rate of 27% at week 4 in the treatment group and 10% at week 4 in the control group. The sample size was calculated by using the “Tests for Two Proportions (Test Version)” module of PASS15 software (NCSS, LLC. Kaysville, Utah, USA) with a one-sided alpha = 0.025, power of 90%, and a 1:1 ratio. In each group, 105 cases will be needed. Considering the lost and rejected cases of 20%, the final minimum number of subjects required for the treatment and control groups will be 132 cases each, and a total of at least 264 subjects will be included.

### Statistical methods

Data will be collected for each study subject at a series of dynamic time points by the use of standardized and structured questionnaires. And then three databases will be created for this study, which are the Full analysis set (FAS), the Per-protocol set (PPS), and the Safety set (SS). For each study group of the trial, missing values were filled using the last observation carryover method, i.e., data from the last obtained data for the missing visit to the end of the observation at all time points. Statistical analyses will be performed using SAS 9.4 software (SAS Institute Inc., Cary, North Carolina 27513, US). Continuous variables are expressed as mean ± standard deviation or median (interquartile range), and categorical variables are represented by frequency (constitutive ratio). The significance level will be set at 5% (*p* < 0.05) with a 95% confidence interval.

(1) Data analysis of primary outcome: The primary outcome in the study is the treatment response rate, which is qualitative data. The treatment response rate at week 4 will be compared between the two groups by the CMH (Cochran’s and Mantel-Haenszel statistics) test, to ensure the effects of different treatment factors on the treatment response rate.(2) Data analysis of secondary outcome: Among the secondary indexes, treatment response rate, treatment remission rate, SE with sleep diary and actigraphy, and weekly usage of remedial drugs are all qualitative data measured repeatedly, so generalized estimating equations will be used for statistics. The mean changes of ISI, SOL/WASO/EMA/TST in sleep diary, TST/SA/WASO/AA in Actigraphy, GAD, PHQ and QLQ-C30 scale are all quantitative data, therefore mixed-effects models will be used for statistics.(3) Data analysis of safety indicators: the incidence of adverse events and medication use are qualitative data, so the chi-square test or Fisher’s test will be used for statistics.

In the process of baseline data collection before conducting the study, we added some covariates, such as anxiety, depression, age, and treatment of breast cancer. When the whole study is completed, *post hoc* analysis will be done to compare the therapeutic effects among different subgroups. To be specific, the stratified CMH test will be used to test the therapeutic effect of acupuncture on cancerous insomnia in different subgroups of breast cancer treated with different therapeutic schedules (e.g. radiotherapy, chemotherapy).

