**Methods:**

This study was designed as a multicenter, randomized, sham-controlled clinical trial. A total of 264 eligible patients with breast cancer-related insomnia will be randomized into an acupuncture group and a sham acupuncture group in a 1:1 ratio. In the trial, patients in the acupuncture and sham acupuncture groups will receive 12 sessions over a consecutive 4-week period. The primary outcome will be the treatment response rate of Insomnia Severity Index (ISI) at week 4; secondary outcomes include treatment remission rate of ISI, Sleep Efficiency (SE) obtained by the use of Sleep diary, treatment response rate of ISI at 8th and 16th weeks of follow-up, the mean changes of ISI, Generalized Anxiety Disorder Scale (GAD-7), Patient Health Questionnaire-9 (PHQ-9), Quality of Life Questionnaire - Core 30 (QLQ-C30), sleep parameters recorded in Actigraphy and weekly usage of remedial drugs. Adverse events will be recorded throughout the study. All analyses will be based on the ITT principle and performed with SAS 9.4 statistical software.

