## Methods

### Study design

This study is a multicenter, randomized, single-blind, sham acupuncture controlled trial, which will be conducted at 6 centers, including LongHua Hospital Shanghai University of Traditional Chinese Medicine, Yueyang Hospital of Integrated Traditional Chinese and Western Medicine of Shanghai University of Traditional Chinese Medicine, Shanghai Seventh People’s Hospital, Hainan Traditional Chinese Medicine Hospital, Affiliated Hospital of Jiangxi University of Traditional Chinese Medicine, and Xuhui District Central Hospital of Shanghai. The study has been approved by the Medical Ethics Committee of LongHua Hospital Shanghai University of Traditional Chinese Medicine (No. 2022LCSY032) and registered at ClinicalTrials Registry (NCT05510700). We will recruit 264 patients who meet the inclusion criteria and assign them to the acupuncture and sham acupuncture groups in a 1:1 ratio. The treatment will last 4 weeks in both groups, followed by a 12-week follow-up. A flow chart of the trial procedures is illustrated in **Figure 1** and **Table 1** with a detailed description of the study procedures and data collection.

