## Outcomes

### Primary outcome

The Primary outcome is the treatment response rate (39, 40), which is the percentage of people whose ISI score decreased by ≥8 points at the end of week 4 treatment compared to the baseline score.

As a subjective and validated measure, the Insomnia Severity Index (ISI) assesses various aspects of sleep, including the onset of sleep, maintenance, early awakening, dissatisfaction, interference with daytime functioning, life quality, and mental distress. The scores are 0 to 4, with a total score range from 0 to 28. Higher scores indicate more severe insomnia. ISI levels can be classified as absence of insomnia (0 to 7), sub-threshold insomnia (8 to 14), moderate insomnia (15 to 21), and severe insomnia (22 to 28).

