To provide a more reliable clinical basis for the acupuncture treatment of breast cancer-related insomnia, we consulted oncologists, psychiatrists, and statisticians for the study design. Consequently, we have made some improvements to the current study. Firstly, this study is designed as a multicenter randomized controlled study. In this study, six study centers are selected from three different regions of China, which will significantly reduce the risk of regional bias. Secondly, our treatment group will use a simple hand acupuncture method without combining other treatments such as electroacupuncture and auricular acupuncture. With this design, acupuncture alone can be evaluated directly for the treatment of breast cancer-related insomnia, without being confounded by other treatments. Clinically effective and commonly used acupoints are selected based on the findings of the preliminary study (59, 60). Thirdly, the control group in this study will be set up as a sham acupuncture group. Such a control group design can be used to verify the effect of needling - a real therapeutic effect or just a placebo effect and make needles less detectable to the patient. Fourthly, considering the complex psychological conditions of breast cancer patients, we won’t completely prohibit patients from taking medications for insomnia in the trial but will adopt a remedial design that allows patients to take medications according to their conditions with no restrictions of the types of medications or the doses taken if they experience serious physical discomfort due to insomnia for 2 or more consecutive days, which prevents patients from additional mental and psychological stress caused by the fear of not being able to take medication for a long period. However, we will include the patients’ medication dosage as a secondary indicator for this trial to be observed. Hence, patients will be asked to keep a detailed record, including the name of the medication, the time of administration, and the dose taken. Fifthly, our current study focuses on observing the clinical effects of 4-week acupuncture treatment and we will add a time point for assessment during the first week of treatment and use a combination of subjective scales and objective recorders to assess the short-term onset of acupuncture and the clinical efficacy at the end of treatment at week 1 and 4 of acupuncture treatment. If the therapeutic effect of acupuncture can improve the patient’s sleep within a short period, it will be crucial to build the patients’ confidence in follow-up treatment, reduce the use of medication, improve the life quality and compensate for the long-onset of other treatment methods. Finally, we will provide completely free acupuncture treatments for patients during the study period. In addition, patients will be provided with sleep hygiene instructions throughout the study. The investigators will communicate with each patient promptly, actively educate them on sleep hygiene instructions, and conduct appointment-based visits and regular follow-ups. These methods will not only reduce the burden of treating patients but also improve their compliance for the smooth implementation of the study. In conclusion, we hope that the results of this study will provide high-quality evidence for the clinical application of acupuncture in the treatment of breast cancer-related insomnia.

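### A single last-observation-carried-forward rule for every outcome makes a missing week-4 ISI a non-response by default and biases the follow-up estimates in a direction that depends on when patients drop out

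*Protocol article*

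**What the plan says.** Protocol article, Statistical methods: "missing values were filled using the last observation carryover method", explained as "data from the last obtained data for the missing visit to the end of the observation at all time points". No outcome is excepted, and no other method for missing data is named. The same section then assigns the CMH test to the primary outcome, GEE to the repeated binary outcomes and mixed-effects models to the continuous ones. The abstract adds "All analyses will be based on the ITT principle".

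The primary outcome is "the percentage of people whose ISI score decreased by ≥8 points at the end of week 4 treatment compared to the baseline score". For the secondary ISI outcome the schedule reads "The mean changes of ISI (40) from baseline. It will be evaluated at weeks 4, 8 and 16", and Table 1 shows no ISI outcome between baseline and week 4. GAD-7, PHQ-9 and QLQ-C30 are taken at weeks 0 and 4 only.

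Study design: "The treatment will last 4 weeks in both groups, followed by a 12-week follow-up". Weeks 8 and 16 are therefore off treatment.

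Sample size calculation: 105 per group for 27% v 10%, raised to 132 per group for loss ("Considering the lost and rejected cases of 20" per cent).

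**The concern.** LOCF takes its meaning from the visit schedule. For the primary outcome, the only earlier ISI is baseline. The filled change is 0, short of the 8-point threshold, so the participant becomes a non-responder. That can be a legitimate deliberate choice. Here it is an unstated by-product of a general rule, and it makes the primary comparison depend on dropout by arm as well as on efficacy.

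At weeks 8 and 16, a participant seen at week 4 and missing at week 8 has her end-of-treatment score copied into the period after needling has stopped. Those visits exist to show whether benefit lasts, and for her the rule assumes the answer. A participant lost before week 4 instead carries baseline, which pulls the other way.

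Mixed models use incomplete records directly and are valid when data are missing at random. Filling the data first discards that property and treats each filled value as an observation.

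**Working it through.** **1. The plan's own figure.** Inputs from Sample size calculation: 27% v 10%, one-sided 0.025, power 90%, 1:1. Unpooled normal formula:

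n = (1.960 + 1.282)² × (0.27×0.73 + 0.10×0.90) / 0.17² = 104.4, so 105 per group. Then 105/0.8 = 131.25, so 132. Both figures reproduce; the pooled formula gives 108.

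**2. Primary outcome, equal loss.** If a share d of each arm has no week-4 ISI and is kept as non-responding, the response rate p becomes p(1 − d). With d = 0.20:

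- acupuncture 0.27 × 0.8 = 21.6%; sham 0.10 × 0.8 = 8.0%; the difference falls from 17.0 to 13.6 points.
- Power = Φ[(Δ − 1.96·SE₀)/SE₁], with SE₀ pooled and SE₁ unpooled.
- 132 per arm under LOCF: SE₀ = 0.0437, SE₁ = 0.0429, power 88.0%.
- 105 completers per arm at 27% v 10%: SE₀ = 0.0536, SE₁ = 0.0523, power 89.3%.

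The like-for-like cost is 1.3 percentage points. If only 10% are lost before week 4, the rates are 24.3% v 9.0% and power is 92.0%. These calculations ignore stratification by centre.

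**3. Primary outcome, unequal loss.** The splits below are assumptions; the article gives a single 20%. All use 132 per arm.

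| True response (acupuncture v sham) | Missing (acupuncture v sham) | Analysed rates | Result |
|---|---|---|---|
| 27% v 10% | 25% v 15% | 20.25% v 8.5% | power 78.0% |
| 27% v 10% | 15% v 25% | 22.95% v 7.5% | power 94.2% |
| 10% v 10% | 10% v 30% | 9.0% v 7.0% | two-sided rejection 9.2% |
| 20% v 20% | 10% v 30% | 18.0% v 14.0% | two-sided rejection 14.3% |

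The nominal two-sided rate is 5%. With a milder 15% v 25% split and 10% true response in both arms, rejection in favour of acupuncture is 4.8%, against a nominal 2.5%.

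**4. Follow-up ISI means.** Assume 20% cumulative loss, split equally over the three intervals (before week 4, weeks 4 to 8, weeks 8 to 16), so 1/15 of each arm in each.

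- Effect fades (3 points at week 4, 1.5 at week 8, 0 at week 16): LOCF gives (1/15)×0 + (1/15)×3 + (1/15)×1.5 + (12/15)×0 = 0.30 points, where the truth is 0.
- Effect maintained at 3 points: LOCF gives (1/15)×0 + (14/15)×3 = 2.80, where the truth is 3.00.

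Simulation of the fading case (132 per arm, SD 5, correlation 0.6, ANCOVA at week 16) gave a spurious benefit of 0.22 to 0.31 points, depending on dropout timing. LOCF rejected in 7.8% to 10.2% of runs, against 4.7% to 5.5% on observed data. With no effect at any visit, LOCF rejected in about 5%.

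**The case against.** The strongest reply is that little harm follows at the planned dropout. Equal loss costs 1.3 points of power and dilutes the difference; it does not inflate type I error. Non-responder imputation is a defensible primary rule for a binary outcome. The larger figures rest on dropout splits that the article does not contain. All of this stands, and it limits the severity.

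It can also be said that sensitivity analyses commonly sit in an SAP that is not shown. That is fair, but the point here is a method the article states without restriction, not one it leaves out.

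A reader might infer more than the text supports:

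- *Every week-4 dropout becomes a non-responder.* The full analysis set is named but not defined in the article. If it requires a post-baseline ISI, such a participant is excluded instead. The statement holds for those retained.
- *The sample size is wrong, or describes a different population.* The arithmetic reproduces, inflating for loss is conventional, and a per-protocol set is also planned.
- *LOCF always flatters durability.* It does so when the effect fades and losses fall after week 4. It understates a maintained effect. Someone missing only week 16 carries a week-8 score, which is already off treatment.
- *The standard errors in the secondary models are too small.* No figure supports this. Rejection stays near 5% when there is no effect, so the excess in the fading case reflects bias.
- *A week-1 ISI is implied by the Discussion*, which says the trial will "use a combination of subjective scales and objective recorders to assess the short-term onset of acupuncture". The sleep diary is already a subjective measure in week 1, and Table 1 and the outcome list schedule no ISI then.

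**Conclusion.** The concern holds and should be fixed. LOCF at all time points is the only stated rule, and it feeds all three types of analysis. For participants retained without a week-4 ISI it amounts to undeclared non-responder imputation. At equal 20% loss before week 4 the cost is small: 88.0% power against 89.3%. If loss differs by arm, the rule alone can create or hide a primary difference. Two-sided rejection of about 9% to 14% under no effect rests on an assumed 10% v 30% split and on true response of 10% to 20% in both arms.

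The follow-up estimates are biased in a direction set by dropout timing and by whether the effect lasts: about 0.3 ISI points too favourable under assumed full decay, and about 0.2 too unfavourable (2.80 v 3.00) if 3 points are maintained. These are modest amounts on a 0 to 28 scale and concern secondary outcomes. The loss of the mixed models' missing-at-random handling does not depend on any of these scenarios.

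**What to change.** Remove LOCF from Statistical methods and replace it with:

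- **Continuous outcomes:** fit the mixed models to the observed data, with no prior filling.
- **Response and remission at weeks 8 and 16 (GEE):** multiply impute the ISI score within each arm, using baseline ISI, centre and the weekly diary data already collected as predictors. Then derive response and remission from the imputed scores.
- **Primary outcome:** name one rule, either the same multiple imputation or deliberate non-responder imputation. Report the other as a sensitivity analysis, together with a delta-adjusted tipping-point analysis. If non-responder imputation is chosen, state that planned power at 20% equal loss is about 88%.

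The choice between the two primary rules is one between acceptable methods; what matters is that it is explicit and made before unblinding. The cost is protocol wording and some extra programming. No additional patients, visits or questionnaires are needed.

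### GAD-7, PHQ-9 and QLQ-C30 have a single post-baseline value, so the mixed-effects model named for them, plainly read, gives only an unadjusted change-score comparison; adjusting week 4 for baseline would be more precise at no cost

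*Protocol article*

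**What the plan says.** - **Model.** In Statistical methods, item (2), the scales are grouped with the ISI changes and the diary and actigraphy times: "GAD, PHQ and QLQ-C30 scale are all quantitative data, therefore mixed-effects models will be used for statistics". Fixed effects, random effects and the role of week 0 are not given. The sentence just before it justifies generalized estimating equations for the categorical outcomes by their being measured repeatedly. For the continuous outcomes the only reason given is that they are quantitative.
- **Schedule.** For each of GAD-7, PHQ-9 and QLQ-C30 the Secondary outcome section says "It will be evaluated at weeks 0 and 4". Table 1 agrees.
- **Form of the outcome.** The abstract lists "the mean changes of ISI, Generalized Anxiety Disorder Scale (GAD-7), Patient Health Questionnaire-9 (PHQ-9), Quality of Life Questionnaire - Core 30 (QLQ-C30" among the secondary outcomes, so the scales can be read as changes.
- **Covariates.** Statistical methods reports that "we added some covariates, such as anxiety, depression, age, and treatment of breast cancer". The only use it then describes is a post hoc comparison of subgroups.
- **Missing data.** "missing values were filled using the last observation carryover method".

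**The concern.** Repeated measurement is what calls for a mixed model; a continuous scale alone does not. These three scales have one value after baseline, hence one change per patient, and nothing is repeated after treatment starts. The usual gain from a mixed model with incomplete follow-up is also unused, because gaps are filled by carrying the last value forward.

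Precision is what is at stake. These are the trial's only listed measures of anxiety, depression and quality of life. The baseline score is already collected, and the plain readings of the text do not use it to reduce variance.

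**Working it through.** **The plan's own figure.** The document gives no design figure for these scales. Its only one is the sample size for the primary outcome, and it reproduces: with unpooled variance, (1.960 + 1.282)² × (0.27 × 0.73 + 0.10 × 0.90) / 0.17² = 104.4, so 105 per group; 105 / 0.80 = 131.25, so 132. It does not bear on this point except to supply 105 per arm as a working size.

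**Inputs.** From the document: two visits (weeks 0 and 4) and 105 per arm. Assumed: equal variance s² at both visits, and a baseline to week-4 correlation r of 0.3, 0.5 or 0.7.

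**Reading 1, change score as response.** There is one row per patient, so the patient variance and the residual variance enter only as a sum. A test fit with a patient random effect split the total into two equal parts (0.616 and 0.616), which is arbitrary. What remains is a two-group comparison of changes.

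**Reading 2, both visits as responses with free baseline means.** With two visits per patient, the group-by-time term is the difference in mean change, the same estimate as in reading 1.

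**Variance per patient.**
- Change score: 2(1 − r)s²
- Week 4 adjusted for baseline (ANCOVA): (1 − r²)s²
- Ratio, ANCOVA to change: (1 − r²) / [2(1 − r)] = (1 + r)/2

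| r (assumed) | Change | ANCOVA | Ratio | Variance cut | SE cut | Inverse ratio |
|---|---|---|---|---|---|---|
| 0.3 | 1.40 | 0.91 | 0.65 | 35% | 19% | 1.54 |
| 0.5 | 1.00 | 0.75 | 0.75 | 25% | 13% | 1.33 |
| 0.7 | 0.60 | 0.51 | 0.85 | 15% | 8% | 1.18 |

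The SE cut is 1 − √ratio, for example 1 − √0.75 = 0.13. The inverse ratio is the variance of the change score relative to ANCOVA. The gain shrinks as r rises: at r = 0.9 the ratio is 0.95.

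**Check by simulation.** 300 trials, 105 per arm, r = 0.5, true difference −0.4 SD.

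| Analysis | Mean estimate | Empirical SE |
|---|---|---|
| Change score | −0.401 | 0.141 |
| Two-visit mixed model, free baseline means | −0.401 | 0.141 |
| ANCOVA | −0.400 | 0.123 |
| Two-visit mixed model, common baseline mean | −0.400 | 0.123 |

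All four are unbiased. The first two coincide, and the last two share the smaller standard error.

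**In power terms.** For an assumed true difference of 0.4 SD at 105 per arm and two-sided 5%, power for change score against ANCOVA is 69% against 86% (r = 0.3), 83% against 92% (r = 0.5) and 96% against 98% (r = 0.7).

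**The case against.** The strongest reply is that this is one sentence on secondary outcomes in a condensed article, and that model terms are commonly left to a statistical analysis plan, which is not shown. That stands: the absence of a named baseline covariate is silence and cannot be read as a decision to omit it. The point rests on what is written, namely a repeated-measures method assigned by data type to outcomes with one post-baseline value. It is also fair that the Secondary outcome section attaches mean change explicitly only to the ISI; the change reading of the scales comes from the abstract and a possible reading of Statistical methods.

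Three stronger readings are tempting, and the document supports none of them.

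- **A reader might infer that a mixed model cannot be fitted to these scales.** It can. Weeks 0 and 4 can both be responses with a patient effect. A random effect for centre, the stratification factor, is also estimable, even on change scores.
- **A reader might infer that the baseline is wasted under every version of the model.** It is not. A model with a common baseline mean matches ANCOVA, and a mixed model with baseline as covariate is compatible with the text. The text simply does not specify either.
- **A reader might infer that the treatment effect would be halved**, because a group main effect averaged over weeks 0 and 4 mixes in a visit before treatment. Nothing says such an average will be reported, and an outcome defined as a change points away from it.

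For the diary times (weeks 0 to 4) and actigraphy times (weeks 0, 1 and 4) a mixed model is suitable, since they are repeated after baseline. Only the role of week 0 is open there.

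**Conclusion.** The point holds as a minor one. The reason given for the model does not match the schedule of these three scales. Under the two plain readings the analysis is the unadjusted change-score comparison, with variance 1.18 to 1.54 times that of a baseline-adjusted analysis for r from 0.7 down to 0.3. This rests on an assumed correlation and equal variances at the two visits. Precision alone is affected: randomization keeps the change-score estimate unbiased. Secondary outcomes only are concerned; the week-4 response analysis and the sample size stand as they are.

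**What to change.** In Statistical methods, item (2):

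- For GAD-7, PHQ-9 and each QLQ-C30 score, replace the mixed-effects model by an analysis of covariance of the week-4 score on treatment, with the patient's own baseline score as covariate. If a mixed model is preferred, specifying a common baseline mean for the two groups gives the same precision.
- For the diary and actigraphy times, keep the mixed model. Take the post-baseline weeks as outcomes (diary weeks 1 to 4, actigraphy weeks 1 and 4) and the week-0 value as covariate.

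The cost is one or two sentences. No new data, visits or patients are needed, because every baseline value is already scheduled at week 0.

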## Discussion

With the continuous advances in medical diagnostic techniques and treatments (47), and as the increasing aging of the population (48), the survival of breast cancer patients will gradually increase and the number of long-term cancer survivors will continue to grow. Insomnia seriously affects the life quality of breast cancer patients (49). As a result, how to better settle the problem is not only the goal pursued by patients, families, and even society, but also the focus of many doctors and researchers. Currently, pharmacotherapy is more commonly used to treat patients with breast cancer-related insomnia, but there are certain potential risks. Furthermore, there is limited data to provide a sustained beneficial effect of long-term drug therapy in patients with breast cancer-related insomnia (50, 51). Yoga (52) and CBT (23, 53) have also been suggested to improve insomnia symptoms in cancer patients, but these methods often require more time from the patient (23) and have a slower onset of action (23), making their action somewhat limited. Acupuncture, a non-pharmacological therapy, that is in line with the socio-psycho-biomedical model of modern medicine, is now widely used in clinical practice for the treatment of insomnia (29–31). Although some studies focused on acupuncture for breast cancer-related insomnia (33, 54–56), there are still limitations. Previous single-arm studies initially validated acupuncture’s clinical efficacy in treating breast cancer-related insomnia (57). Recently, two randomized controlled single-blind trials compared acupuncture with placebo acupuncture to assess its efficacy. One trial focused on chemotherapy-complicated patients (33), while this study included patients at any treatment stage. This analysis could guide tailored treatment decisions. Another study assessed acupuncture’s efficacy for breast cancer-related insomnia using only the Pittsburgh Sleep Quality Index (58), while this study used multiple assessment tools for a comprehensive evaluation.

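### The subgroup comparison is assigned a stratified CMH test, which does not compare effects between subgroups on either reading of the sentence (minor)

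*Protocol article*

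**What the plan says.** The last paragraph of Statistical methods in the protocol article states an aim and a method in consecutive sentences. The aim is a post hoc exercise at study end: "analysis will be done to compare the therapeutic effects among different subgroups". The method follows as the specific form of that aim: "the stratified CMH test will be used to test the therapeutic effect of acupuncture on cancerous insomnia in different subgroups". The subgroups are described by example, as "subgroups of breast cancer treated with different therapeutic schedules (e.g. radiotherapy, chemotherapy", after a sentence on baseline data that reads "we added some covariates, such as anxiety, depression, age, and treatment of breast cancer".

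The same section uses CMH for the primary analysis: "The treatment response rate at week 4 will be compared between the two groups by the CMH". The article names no homogeneity test and no arm-by-subgroup interaction term anywhere.

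**The concern.** Comparing effects among subgroups is a question about heterogeneity: is the arm difference in one subgroup different from that in another? The CMH statistic answers another question, namely whether there is an association between arm and response once the strata are combined. It can be strongly significant when subgroups respond identically, and just as significant when only one subgroup responds.

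A significant stratified CMH could then be taken as a subgroup finding although it largely restates the overall result. If separate tests are run per subgroup, a significant result in one and a non-significant result in another could be taken as a difference in effect that the data do not establish.

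**Working it through.** **Inputs from the article (Sample size calculation).** Response rates: "treatment response rate of 27% at week 4 in the treatment group and 10% at week 4 in the control group". Design: "with a one-sided alpha = 0.025, power of 90%, and a 1:1 ratio". Also 105 evaluable per group, 20% loss, and 132 randomized per group.

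**Planned sample size.** Two proportions, unpooled variance:
n = (1.960 + 1.282)² × (0.27×0.73 + 0.10×0.90) / 0.17² = 10.507 × 0.2871 / 0.0289 = 104.4, so 105. Then 105 / 0.80 = 131.25, so 132. The plan's figures reproduce and are not in dispute.

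**Assumptions.** The article gives no subgroup sizes or subgroup rates. I assume two equal subgroups, so 132 / 2 = 66 per arm in each, or 52 per arm if only about 105 per group are evaluable. Tests are two-sided at 5%.

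**Reading 1: subgroup is the stratum.**
CMH χ² = [Σ(a − E)]² / ΣV, where a is the number of acupuncture responders, m the total responders in the stratum, E = m/2 (equal arms), and V = m(132 − m) / (4×131).

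| | A: same effect | B: effect in one subgroup |
|---|---|---|
| Subgroup 1 | 18/66 v 7/66 | 29/66 v 7/66 |
| Subgroup 2 | 18/66 v 7/66 | 7/66 v 7/66 |
| Σ(a − E) | 5.5 + 5.5 = 11 | 11 + 0 = 11 |
| ΣV | 5.105 + 5.105 = 10.21 | 6.595 + 3.153 = 9.75 |
| CMH χ² | 121/10.21 = 11.85 | 121/9.75 = 12.41 |
| CMH p | 0.0006 | 0.0004 |
| Mantel-Haenszel common OR | 3.16 | 3.16 |
| Subgroup ORs | 3.16 and 3.16 | 6.61 and 1.00 |
| Breslow-Day p | 1.0 | 0.008 |

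The numerator is the same in both columns because CMH sums the departures over strata and does not record where they arose. Breslow-Day separates the two cases.

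Simulated rejection rates at 66 per arm per subgroup:

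| True rates | CMH | Breslow-Day |
|---|---|---|
| 27% v 10% in both | 96% | 6% |
| 44% v 10%; 10% v 10% | 96% | 74% |
| 27% v 10%; 10% v 10% | 51% | 36% |

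The first two rows share the same average: (44% + 10%) / 2 = 27%.

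**Reading 2: a CMH within each subgroup, stratified by centre.** Centre sizes are not given, so each subgroup was treated as a single table. With 27% v 10% truly holding in both subgroups, each separate test is significant about 73% of the time at 66 per arm. The chance that exactly one of two independent tests is significant is 2 × 0.73 × 0.27 = 0.39, and simulation gives about 40%. At 52 per arm it is 47%. So identical effects produce an apparent contrast in two trials out of five or more.

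**Power of the right question.** If the effect is 27% v 10% in one subgroup and absent in the other, power to detect heterogeneity is about 36% at 66 per arm (Breslow-Day). Allowing for 52 per arm and a more conservative heterogeneity test, it falls to about 27%.

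**The case against.** The best defence is that the sentence is ambiguous. Centre is the randomization stratum and CMH is already the primary test, so the text may mean a centre-stratified CMH inside each subgroup. Each subgroup would then have its own result, and it would be wrong to say that the analysis yields only one pooled answer. This stands as a limit on the first reading, but it does not rescue the plan: separate p-values are not a comparison, and the 40% to 47% disagreement under identical effects shows the consequence.

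Other defences also stand. The analysis is labelled post hoc; the primary test and sample size do not depend on it; and the heterogeneity test would miss a moderate difference about two times in three.

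A reader might infer more than the document supports:

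- That CMH would hide opposite effects. It would under the first reading, but nothing in the article suggests that acupuncture reduces response in any subgroup, so that case should not set the size of the point.
- That the post hoc label is contradicted by pre-specification. The covariates and schedules are given only as examples, without a closed list, categories or cut-points. Calling them pre-specified would overstate what is fixed.
- That the article promises tailored care from this test. The Discussion says "This analysis could guide tailored treatment decisions", but that sentence follows a contrast with a trial in patients having chemotherapy and does not name the subgroup CMH.

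**Conclusion.** The point holds as a mismatch between a stated aim and the test named for it. This is not a detail left to an analysis plan, because the article itself fixes both. Under the first reading the test gives the same answer, about 96% rejection, whether the effect is shared or confined to one subgroup. Under the second, it gives discordant subgroup results in about 40% to 47% of trials when there is no difference to find.

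The sizes rest on two equal subgroups, the article's 27% and 10% rates, an illustrative 44% for the concentrated effect, and no centre effects. Other splits would change the percentages but not the fact that neither procedure tests heterogeneity. The severity is minor: the primary analysis is untouched and the subgroup work is exploratory.

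**What to change.** For the subgroup comparison, replace the stratified CMH test with one of two options: a test of homogeneity of odds ratios (Breslow-Day), or a logistic model for week 4 response containing arm, subgroup and arm-by-subgroup only. Report the heterogeneity p-value with the risk difference and 95% confidence interval in each subgroup, and label the results exploratory. If a CMH is kept for estimates within subgroups, say what its strata are.

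Keep the model small. At the planned rates there would be about 105 × (0.27 + 0.10) = 39 responders among those evaluable, or 132 × 0.37 = 49 among all randomized. The mismatch can be corrected without centre or baseline ISI terms, and those counts would support them poorly.

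The cost is a wording change, with no new data and no change to sample size. The downside is low power, about 27% to 36% in the moderate scenario above. The text should therefore say that a non-significant interaction is not evidence of equal effects.
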